## Inclusion and Exclusion Criteria

All 147 HMS providers will be eligible to be included in the study, with summary data of all adults ( $\geq 18$  years old) admitted to the HMS at either Emory University Hospital (EUH), Emory University Hospital Midtown (EUHM), Emory Johns Creek Hospital (EJCH), or Emory St. Joseph's Hospital (ESJH)

## Population.

HMS providers do not overlap with any of the special populations identified by the IRB template. Moreover, the patient data summarized is agnostic to any of the identified special populations.

## Vulnerable Populations

The sole purpose of this study is to evaluate impact of peer-comparison of prescribing data to HSM providers on reducing high rates of antibiotic prescribing. This study is not designed to specifically address or analyze prisoners or other vulnerable populations, and this is not a focus of the research. Our dataset will not identify if the patient is a prisoner, employee or cognitively impaired so it is possible that some of these vulnerable individuals will be included in the retrospective datasets.

## Local Number of Participants

All 147 HMS providers will be eligible to be included in the study.

## Recruitment Methods

The Department of Hospital Medicine will work with study team to socialize this QI initiative with all HMS providers to inform them of the process. The Department will consider this a QI initiative and all HMS providers will participate in the initiative as a QI initiative, so no recruiting materials will be utilized. However, in the 4 months leading up to the launch of the study a web-site will be launched with initiative information and a description of this study as a means to study the impact of the intervention. Two emails

will be sent by the Division Leadership with the website address and an invitation for staff to view the information. We have submitted draft contents of this website with this protocol submission.

## Withdrawal of Participants

None anticipated since this is a QI initiative with oversight by HMS and the Stewardship Research Team.

## Risk to Participants

There are no foreseeable risks to the HMS providers, except perhaps perceptions by peers being altered if the providers share his/her prescribing metrics and rankings.

Risk to patients cared for by the HMS providers are not foreseeable as well, as all providers will continue to practice best care and no specific treatment recommendations are coming from any aspect of this QI. Only provision of educational resources based on current EHC standards of practice

The only risk to study participants is the possibility for a breach of confidentiality via accidental disclosure of identifiable information. However, as detailed above, we will take all necessary precautions to ensure data is securely stored in a HIPAA compliant manner and only trained and approved study investigators will have access to this data.

## Potential Benefits to Participants

HMS providers will likely benefit from this formal evaluation of the QI by receiving summary data on the impact the intervention had on their prescribing habits and patient outcomes.

## Compensation to Participants

none

## Data Management and Confidentiality

All data from this study will be stored in a secure folder on the Emory OneDrive/Teams for Business platform that is HIPAA approved and supported by the Emory Office of Information Technology. No patient-specific data will be included as part of the data set at any point, only summary counts of encounters with specific patient mix indicators and days of therapy during the encounter.

Provider specific data will be included, including name. Provider identifies are needed to remain with the bimonthly metric data to allow accurate feedback of data to the correct provider. Only approved study investigators that have completed all required CITI trainings will be allowed access to the datasets. Data will be kept for 3 years after study completion and until all manuscripts have been published and the IRB is closed out.

(Add your text)

## Provisions to Monitor the Data to Ensure the Safety of Participants

**There is no more than minimal risk to participants.**

## Provisions to Protect the Privacy Interest of Participants

Participants will have an opportunity to participate in focus groups and Departmental meetings to provide feedback to the study team, in a town hall format. The Department of Hospital Medicine will work with study team to socialize this QI initiative with all HMS providers to inform them of the process.

## Economic Burden to Participants

None

## Informed Consent

We are requesting a waiver of consent for this research.

Regarding HMS providers – Our research study will have no direct effect on patient care, as the QI feedback involves data from the previous 2 months with an intent to improve the providers understanding of best practice. Considering this is a QI initiative with HMS and the Antibiotic Stewardship Teams, it involves no procedures for which written consent is normally required outside of the research context.

Regarding patient data, given the retrospective nature of the study and very large number of patients that will be included in the dataset, it would be impractical, if not impossible to contact all participants for consent. We will exclude all minors (<18 years old) in the dataset. Also, all patient data remaining in the bi-monthly dataset is summarized among all encounters at the provider level, with no ability to track back any specific antibiotic use to any specific patient.

## Setting

Emory University Hospital (EUH), Emory University Hospital Midtown (EUHM), Emory Johns Creek Hospital (EJCH), or Emory St. Joseph's Hospital (ESJH)

## Resources Available

- Our study team includes members of the Quality Office with access to the required data and capacity to produce the bi-monthly metric. We have dedicated project management staff and study staff to implement this study as part of our CDC funded Epicenter (PEACH) funded through the cooperative agreement outlined earlier in this protocol
- The Division of Hospital Medicine Chief and Chief Quality Officer are aware of this study and supportive of this formal evaluation of the stated QI activities.

## Multi-Site Research When Emory is the Lead Site

Not applicable

## 1. Study Objective

Inappropriate antibiotic prescribing in both primary care and inpatient settings contributes to antibiotic resistance and associated adverse outcomes like *Clostridioides difficile* infection (CDI) and increased healthcare costs.(C D C 2019; Jit et al. 2020). While antibiotic stewardship interventions, such as provider education and feedback, have shown promise in ambulatory settings, their translation to inpatient care faces unique challenges. **In this study, we aim to determine the impact of using an automated peer comparison report of antibiotic prescribing on hospitalists prescribing rates without negative impact on patient outcomes** in an academic network of hospitals in Atlanta, Georgia.

## 2. Intervention

The intervention will comprise two components: (1) a one-time educational session on antibiotic de-escalation and (2) bimonthly email feedback reports. Educational sessions, led by facility stewardship leads, will focus on evidence-based recommendations for presumed pneumonia and urosepsis, including indications for empiric anti-pseudomonal coverage and use of the hospital's antibiotic prescribing assistance tool. Feedback reports will reinforce these indications and will provide a link to the tool.

Provider-specific feedback reports will use observed-to-expected ratios (OERs), derived in part from EPIC Clarity System clinical and billing data. Generalized linear models will be used to generate OERs, adjusted for the proportions of patients with sepsis, end-stage renal disease, and urinary tract infections. These risk adjustments will be based on a prior study identifying factors consistently associated with broad-spectrum hospital-onset (BS-HO) antibiotic prescribing (Onwubiko et al. 2024).

Bimonthly, the stewardship research team will automatically email private PDF reports to each provider. Report content and formatting will be informed by CP-FIT's key feedback elements and will be assessed through cognitive interviews with 13 providers conducted during the development phase, with corrective changes to be implemented based on structured interview questions.

One week after the third prescribing report is sequentially sent (six months after intervention initiation), the antibiotic stewardship team will email a single-question Microsoft Form survey to providers, seeking confirmation of whether they viewed the previous reports. Non-responders will receive email reminders from the hospital medicine faculty liaison, who will then personally follow up with remaining non-responders to encourage completion.

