## Objectives

Primary Objective: **Determine the impact of using an automated peer comparison of antibiotic prescribing on hospitalists' prescribing rates**

Secondary Objectives:

- 1) Demonstrate no adverse effects on patients cared for by HMS during study period
- 2) Determine variability and predictors of antibiotic prescribing by Hospital Medicine Service (HMS) across four Emory Healthcare Hospitals

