## Study Intervention/Investigational Agent

No Drug or Device is being used for this intervention.

Primary intervention.

The intervention is messaging to hospitalists via email every 2 months (bi-monthly) that contains peer comparison data of the previous 2 months and antibiotic prescribing educational content. Draft content of this message is submitted.

The detail of the content is still to be developed, but may include a relative rank in prescribing metrics, with blinding to specific Peers' identity, with department wide and facility specific goals highlighted. Those in the lowest prescribing quartile will earn the designation of "Top Performer". The usual care arm will be an educational email about simple steps to improve antibiotic prescribing sent bimonthly to all hospitalists.

Secondary Intervention (if needed).

An interim analysis will occur at the facility-level after three quarters (9 months) of intervention data to determine if high prescribers (i.e., SAR above 1.25, or 25% higher than predicted) continue to prescribe high in more than half of the intervention bimonthly prescribing periods. This would be interpreted as a lack of effect to the email-based intervention, and a secondary intervention would be offered to all high prescribers consisting of bi-monthly check in with the stewardship lead (either infectious disease pharmacist or medical director of stewardship) at each facility to provide an open forum for questions and answers about the data and any clinical practices.

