### 3. Study Design

We plan to use a Randomized Step Wedge Cluster Design (R-SWCD) to evaluate the effect of the peer comparison feedback report on antibiotic prescribing (BS-HO group). The study will be conducted in 4 hospitals (clusters) in Atlanta, Georgia. Of note, pending discussion with Hospital Medicine Leadership, the intervention may also be rolled out at an additional hospital, although lack of retrospective data would not allow inclusion of this facility in the full analysis. Hospitals will begin in the control condition and end in the intervention condition, wherein, all hospitals will receive the intervention and cross over to the intervention arm in a random order (Figure 1). Randomization will occur at the hospital level rather than at the provider level to avoid contamination and spillover effects. Providers within a hospital are not fully independent of each other, groups tend to form because of certain selection factors, and so providers tend to be more similar to each other with respect to potential confounders.

Outcomes linked to the same provider will be assessed repeatedly on a bi-monthly bases in each hospital over a two-year time period (2023-2024). Hospitals will cross-over to the intervention arm sequentially, resulting in 4 steps with an equal step length of 2 months. Following a baseline period (January 1 - June 30, 2023), the first cluster will begin the intervention on July 1, 2023. The final cluster will transition by March 1, 2024, with intervention continuing through December 31, 2024 in all hospitals.

A step wedge design, which involves the randomized and sequential roll out of the intervention to hospitals over time was chosen as it can model and adjust for any underlying temporal trends and results in all hospitals receiving the intervention **which is desirable from a healthcare quality improvement and antimicrobial stewardship perspective**. Randomization of the order of implementation reduces confounding from baseline cluster-level factors. Lastly, gradual roll out of the intervention will allow us to identify and address any implementation bottlenecks.

**Figure 1.** Stepped-Wedge interventional study design. Abbreviations: E, educational session; PF, Provider Feedback. Grey boxes reflect intervention periods with bi-monthly PF reports.

|            | 2023       |        |        |        | 2024   |        |               |
|------------|------------|--------|--------|--------|--------|--------|---------------|

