|            | Jan-Jun 23 | Jul-23 | Sep-23 | Nov-23 | Jan-24 | May-24 | Jul to Dec 24 |
| Hospital A |            | E + PF | PF     | PF     | PF     | PF     | PF            |
| Hospital B |            |        | E + PF | PF     | PF     | PF     | PF            |
| Hospital C |            |        |        | E + PF | PF     | PF     | PF            |
| Hospital D |            |        |        |        | E + PF | PF     | PF            |
| Hospital E |            |        |        |        |        | E + PF | PF            |

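### The SAP credits the effect to the peer-comparison report, but an education session starts with the reports at every hospital, so as planned only their combined effect is estimable

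*Combined protocol and SAP*

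**What the plan says.** **What is to be evaluated.** The protocol's primary objective is "Determine the impact of using an automated peer comparison of antibiotic prescribing on hospitalists' prescribing rates". SAP section 1 says "we aim to determine the impact of using an automated peer comparison report of antibiotic prescribing on hospitalists prescribing rates", and SAP section 3 uses the stepped-wedge design "to evaluate the effect of the peer comparison feedback report on antibiotic prescribing (BS-HO group". The SAP title also names peer-comparison feedback alone. The primary model in SAP section 7 has one exposure term, a provider's receipt of feedback reports, and no term for education.

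**What is delivered.** SAP section 2: "The intervention will comprise two components: (1) a one-time educational session on antibiotic de-escalation and (2) bimonthly email feedback reports". Facility stewardship leads run the session, which covers presumed pneumonia, urosepsis and when empiric anti-pseudomonal cover is indicated. The reports repeat part of that teaching: "Feedback reports will reinforce these indications and will provide a link to the tool". Figure 1 marks E (education) and PF (feedback) together in each hospital's first intervention period and PF alone afterwards. The first row begins "Hospital A | | E + PF | PF".

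**What it is compared with.** The protocol, under Study Intervention, says "The usual care arm will be an educational email about simple steps to improve antibiotic prescribing sent bimonthly to all hospitalists". SAP section 3 says only that hospitals start in a control condition. It neither describes that condition nor mentions the email.

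**The concern.** In a stepped wedge, the randomised crossover identifies the effect of whatever changes at that moment. Here two things change: a teaching session on de-escalation, and peer-comparison reports. The primary outcome is days of broad-spectrum therapy per 1,000 billed patient-days, which a session on de-escalation could plausibly lower by itself. SAP section 1 itself lists provider education beside feedback among the stewardship measures that have shown promise.

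If the result is positive, the plan's wording leads to a published claim that automated reports reduce prescribing. Another health system could then adopt the emails without the teaching, on evidence that does not show the emails work alone. The undefined control condition adds a second gap: the reader cannot tell whether the comparison is with no education or with a recurring educational email.

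**Working it through.** The documents give no figure to reproduce. The question is which effects the design can identify.

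**Inputs.** Four hospitals and two-month periods from January 2023 to December 2024, so 12 periods and 4 × 12 = 48 hospital-periods (SAP sections 3 and 5). Figure 1 puts the crossovers in July, September and November 2023 and January 2024. The text of section 3 has the last hospital crossing by 1 March 2024, although four steps two months apart from 1 July 2023 reach 1 January 2024. Both dates were checked. The possible fifth hospital is outside the full analysis, and Figure 1 starts both components together there too.

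**Step 1: count the cells.**

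| Hospital | First intervention period | Control periods | Intervention periods |
|---|---|---|---|
| A | Jul–Aug 2023 (4th) | 3 | 9 |
| B | Sep–Oct 2023 (5th) | 4 | 8 |
| C | Nov–Dec 2023 (6th) | 5 | 7 |
| D, Figure 1 | Jan–Feb 2024 (7th) | 6 | 6 |
| D, March 2024 | Mar–Apr 2024 (8th) | 7 | 5 |

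- January last step: control 3 + 4 + 5 + 6 = 18; intervention 9 + 8 + 7 + 6 = 30.
- March last step: control 3 + 4 + 5 + 7 = 19; intervention 9 + 8 + 7 + 5 = 29.

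**Step 2: compare the two exposures.** Let E = 1 from the session onward (a lasting effect) and PF = 1 from the start of feedback. Following Figure 1, E = PF in all 48 cells, with no education-only and no feedback-only cell.

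**Step 3: rank.** The design matrix has 4 hospital columns, 11 period columns, E and PF, so 17 columns. Its rank is 16 under either last-step date. With E and PF merged into one column there are 16 columns and rank 16, so the combined effect is estimable. Two identical columns stay identical under random facility and provider effects or a log link, so the SAP's negative binomial mixed model does not change this.

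**Step 4: what the single term recovers.** These are log-scale effects. A total of −0.10 corresponds to exp(−0.10) = 0.905, close to the 10% reduction in the protocol's sample-size statement.

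| True E | True PF | Estimate |
|---|---|---|
| −0.10 | 0 | −0.10 |
| −0.05 | −0.05 | −0.10 |
| 0 | −0.10 | −0.10 |

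**Step 5: what would separate them.** These are least-squares variances of the PF effect relative to the combined contrast, on hospital-period values with equal independent errors.

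| Assumption or change | January last step | March last step |
|---|---|---|
| Session effect confined to its first two-month period | 1.56 | 1.42 |
| Feedback starts one full period after the session (4 education-only cells) | 1.09 | 1.20 |
| Session at all hospitals before the first crossover | 1.00 | 1.00 |

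The SAP adopts none of the three.

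**Step 6: when exposure starts.** SAP section 2 places the third report six months after initiation. On a two-month cycle the first report then falls at 6 − 2 × 2 = 2 months, whereas Figure 1 shows feedback from the first period. If exposure is coded by receipt of reports and the first report does come at month 2, four periods that follow the session would count as control: 18 + 4 = 22 control cells (January) or 19 + 4 = 23 (March), 4 of them already educated.

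**The case against.** The strongest reply is that the two components are disclosed openly in section 2 and Figure 1, that testing a combined stewardship intervention is legitimate, and that its effect is estimable. That is right. The fault lies in what the title, objective, exposure label and eventual conclusion claim for it.

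Four other replies stand in part.

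- **The aliasing is conditional.** Figure 1 marks E in only one period per hospital, 4 of 48 cells. If a single session has only a brief effect, the components separate at some cost in variance. A reader might infer that no re-analysis, or no choice of timing, could ever separate them. Step 5 shows that is too strong. The SAP, however, states no such assumption and plans no such analysis.
- **The educational email is not withdrawn.** A reader might infer that the SAP removed the protocol's education control. The SAP is silent and the email may have continued. It would still not be the session, which control periods lack.
- **The protocol's contrast was not pure either.** Its feedback email also carried educational content, and the detail was still to be developed. But education was then present on both sides of the comparison.
- **Some providers may receive reports without the session.** SAP section 4 allows for turnover and a possible analysis of new staff. That would be non-randomised evidence. The same applies to the planned sensitivity analysis in providers who say they reviewed the reports: they are self-selected and received the same combination.

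**Conclusion.** The point holds as a mismatch between the stated objective and what the design identifies. With a lasting session effect and the start dates in Figure 1, education and feedback coincide in all 48 hospital-periods, and the data fix only their sum. The conclusion is the same for a January or a March 2024 last step. No planned analysis divides the sum.

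Three stronger readings are not supported. The trial is not uninformative, because it can estimate the combined effect against the control period. The peer-comparison share of a 10% reduction is not shown to lie between 0% and 10%; that range also needs additive components, neither of which raises prescribing. Nor can one say that the session taught exactly the drugs counted in the outcome: section 2 speaks of anti-pseudomonal indications, and the documents do not list the broad-spectrum hospital-onset agents.

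The control condition is undefined in the SAP and needs to be settled whichever way the objective is worded.

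**What to change.** 1. Restate the title, objective, exposure label and conclusion as the effect of an educational session plus peer-comparison feedback, and say that the effect of feedback alone is not estimated.
2. Define the control condition in SAP section 3 consistently with the protocol's usual-care description, stating whether the bimonthly educational email was sent in control periods, in intervention periods, or both.
3. Code exposure from the start of the combined intervention, that is, each hospital's session date. Reconcile Figure 1 with the six-month timing of the third report in section 2 and with the 1 March 2024 date in section 3.

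Items 1 and 2 cost only wording. Item 3 needs a dated log of sessions and reports by hospital and changes one variable definition.

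An optional design alternative, if timing allows, is to hold the session at all hospitals before the first crossover, so that the reports are the only component switched on at each step. In the simplified calculation the variance is unchanged (ratio 1.00). The contrast may be smaller, because any education effect moves into the control level, and the education-free baseline becomes shorter. It would not exactly recreate the protocol's recurring-email comparator. Because section 2 cites a risk-adjustment study dated 2024, the chance to act before July 2023 may already have passed when this text was written; the wording changes do not depend on it.

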## **7. Statistical Analysis**

**For the primary outcome analysis,** a generalized linear mixed-effects model with a negative binomial distribution and log link will be used to evaluate the effect of the intervention on antibiotic prescribing rates over time. The observed DOT will be modeled as a function of provider receipt of feedback reports, time (bimonthly period) to account for secular trends and time-varying confounding, and a random facility effect to account for clustering of providers within hospitals. A random intercept for each provider nested within facility will be included to account for correlation among repeated observations and the hierarchical data structure. The intra-cluster correlation coefficient (ICC) will be estimated to quantify the proportion of total variance attributable to between-cluster differences. Models will adjust for patient-mix characteristics as covariates.

Sensitivity analyses of the primary outcome will be conducted among the subset of providers who indicate that they received and reviewed the feedback reports, to account for potential implementation bias.

**Secondary outcomes will be analyzed at the patient level** among all patients receiving care from hospital medicine services and discharged with ICD-10 codes for pneumonia or urinary tract infection, as this group is expected to be most vulnerable to changes in antibiotic de-escalation practices. Safety outcomes will be analyzed using generalized mixed-effects logistic regression models to evaluate intervention effects over time, accounting for repeated hospitalizations within patients and clustering by facility. Covariates will include time (to account for seasonality) and patient-level indicators (COVID-19, influenza, Elixhauser comorbidity index, and sepsis). All analyses will be performed using R Statistical Software (version 4.2.0; R Core Team, 2021).

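### With the first report at about month 2, each hospital's first window holds the education session but almost no feedback, and the primary model has no rule for that window

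*Combined protocol and SAP*

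**What the plan says.** SAP section 2 (Intervention) describes a package: "The intervention will comprise two components: (1) a one-time educational session on antibiotic de-escalation and (2) bimonthly email feedback reports". On frequency it says "Bimonthly, the stewardship research team will automatically email private PDF reports to each provider". It dates the third report only in passing, when it schedules a survey on whether reports were viewed: "One week after the third prescribing report is sequentially sent (six months after intervention initiation". No send date is given for report 1.

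SAP section 3 (Study Design) treats the start date as the crossover: "all hospitals will receive the intervention and cross over to the intervention arm in a random order (Figure 1", and "the first cluster will begin the intervention on July 1, 2023". Figure 1 labels each hospital's first box E + PF, and its legend adds "Grey boxes reflect intervention periods with bi-monthly PF reports". For the last hospital the text says "The final cluster will transition by March 1, 2024", while Figure 1 shows Hospital D at January 2024.

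SAP section 7 (Statistical Analysis) defines the primary exposure differently: "The observed DOT will be modeled as a function of provider receipt of feedback reports". It mentions no start-date rule, lag or transition period.

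**The concern.** On the timing in SAP section 2, prescribing in a hospital's first window comes before that hospital's first report but overlaps or follows its education session. The window is neither clean control time nor full intervention time. Read literally, section 7 makes it control, whereas section 3 and Figure 1 make it intervention. One on/off term cannot describe it well under either coding.

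This matters because of where these windows sit. Once all hospitals have started, no concurrent comparison remains, so the intervention effect is informed mainly by the rollout windows. First windows are a third to a half of the intervention cells there. Misdescribing them can shrink the primary estimate well beyond their share of all data. Leaving the coding open also means that it could be chosen after the data are seen.

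**Working it through.** **Inputs from the documents.** Reports every two months, with the third at six months (SAP section 2). Four hospitals, two-month steps, first start 1 July 2023, last start January 2024 (Figure 1) or by March 2024 (section 3 text). Twelve two-month windows from January 2023 to December 2024. A 10% reduction for illustration (protocol, Study Summary, Sample Size).

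**Assumptions.** Equal hospitals; a constant effect from the second window on; a fraction f of it in the first window. Time is taken as categorical or linear, because section 7 does not say which. The hospital share of cell variance runs from 0 to 0.99, and hospital fixed effects are also tried.

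**1. Report calendar.** With report 1 at month k, the third is at k + 4.
- k = 2: reports at months 2, 4, 6. This reproduces the plan's six months.
- k = 1: months 1, 3, 5.
- k = 0: months 0, 2, 4.

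Only k = 2, or a date very close to it, fits. For the first hospital that is about 1 September 2023.

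**2. Cells affected.** Starts in windows 4, 5, 6 and 7 give 9 + 8 + 7 + 6 = 30 intervention cells. A March last start gives 9 + 8 + 7 + 5 = 29. First windows are 4/30 = 13.3% or 4/29 = 13.8%. In windows with both conditions present there are 1 + 2 + 3 = 6 intervention cells, of which 3 are first windows (January), or 1 + 2 + 3 + 3 = 9, of which 3 are first windows (March).

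**3. Full mismatch.** The expected coefficient is the first element of (D'V⁻¹D)⁻¹D'V⁻¹y. Here D holds exposure, time and, where used, hospital effects; V has a hospital random intercept; y is the true pattern on the log scale (0 before the start, f in the first window, 1 after). Let a be the result when the window is coded wholly the wrong way.

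| Time, last start | Coded from start, no effect in window 1 | Coded from window 2, full effect in window 1 |
|---|---|---|
| Categorical, January | 0.280-0.400 | 0.280-0.400 |
| Categorical, March | 0.405-0.538 | 0.405-0.538 |
| Linear, January | 0.433-0.494 | 0.470-0.531 |
| Linear, March | 0.447-0.543 | 0.473-0.569 |

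**4. Partial effect in window 1.** The coefficient is linear in y, so start-date coding gives f + (1 − f)a and window-2 coding gives (1 − f) + f·a.
- f = 0.5, either coding: 0.5 + 0.5 × 0.280 = 0.64 up to 0.5 + 0.5 × 0.569 = 0.785.
- f = 0.75, start-date coding: 0.75 + 0.25 × 0.280 = 0.82 up to 0.75 + 0.25 × 0.543 = 0.886.
- f = 0.75, window-2 coding: 0.25 + 0.75 × 0.280 = 0.46 up to 0.25 + 0.75 × 0.569 = 0.68.

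A plain average over the 30 cells with f = 0.5 would be (26 + 4 × 0.5)/30 = 0.93. The extra shrinkage comes from the weight of the rollout windows.

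**5. On the rate scale.** A true 10% reduction reads as 1 − 0.90^b: 6.5-8.0% for b = 0.64-0.79, 8.3-9.0% for 0.82-0.89, and 2.9-5.8% for 0.28-0.57.

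**6. Unequal hospitals.** With an assumed split of 15/30/40/40 (total 125) in every order, a runs from about 0.20 to 0.60. The half-effect range becomes 0.5 + 0.5 × 0.20 = 0.60 to 0.5 + 0.5 × 0.60 = 0.80.

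**7. Cost of a first-window indicator.** With equal hospitals, the standard error of the report effect, relative to that of the single start-date term, is 1.195-1.250 (categorical, January), 1.140-1.193 (categorical, March), 1.172-1.199 (linear, January) and 1.147-1.188 (linear, March).

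**The case against.** A reader might infer that section 2 and Figure 1 contradict each other. The documents do not prove that. The six-month figure is a parenthesis in a sentence about a survey, and Figure 1 gives boxes, not send days. A report sent in the last days of each window would satisfy both, and six months could also loosely mean three bimonthly cycles. This stands as far as the word contradiction goes. It does not remove the problem: with an end-of-window report, nearly all first-window prescribing still precedes it.

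It can also be said that start-date coding is plainly intended. Section 3 describes crossover in randomised order, and section 7 puts providers who confirm that they reviewed the reports into a separate sensitivity analysis, which suggests that the primary term is not individual receipt. That is the likelier intent, but section 7 does not say so, and start-date coding alone leaves the dilution in place if report 1 comes at about month 2.

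Finally, the stated aims in SAP sections 1 and 3 concern the feedback report, so receipt coding could be defended. But it would place the education session in the control condition and step away from the randomised start. A separate first-window term serves that aim better.

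**Conclusion.** The point holds in conditional form. If report 1 goes out at about month 2, as section 2 implies, a single exposure term misdescribes the first window whenever that window carries part of the effect. How much it carries is unknown. With half the effect there, the primary estimate is about 0.64-0.79 of the true log effect under either coding. With 75% there and start-date coding, it is 0.82-0.89.

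A tempting stronger reading is that the trial will recover only 0.28-0.57 of its effect. That needs either no effect of education in the first window under start-date coding, or the full effect before any report under receipt coding. The documents support neither extreme. At the other end, the bias is nil if report 1 is sent on the start date and acts at once, which baseline data from January 2023 would allow.

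The sizes rest on equal hospitals, a constant effect after the first window, and a simple hospital-by-window model on the log scale. The sponsor should make the change; confidence is medium because the send date is inferred.

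**What to change.** - **SAP section 7:** define primary exposure from each hospital's randomised start date, in place of provider receipt. The primary estimate is then the effect of the randomised package of education plus reports. This needs no new data and costs the primary analysis no precision, but it does not by itself remove the dilution.
- **SAP section 7, unless report 1 is sent on the start date:** pre-specify a secondary analysis that gives the first window its own indicator or treats it as a transition period. This estimates the report-period effect without the dilution. With a separate indicator, the standard error is about 14-25% larger (equal hospitals), which is why it should be secondary.
- **SAP section 2:** state when report 1 is sent relative to each hospital's start. Change six months to four only if report 1 goes out on the start date; in that case the secondary analysis is not needed.

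In all, this is one line in section 2 and one or two in section 7.
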